### Ethics Approval

The study protocol has been reviewed and approved by the Ethic Review Board of Dipartimento di Scienze della Formazione Sezione di Psicologia at the University of Catania on November 25, 2020 (Ref 104/20).

### Population

This study plans to recruit approximately 750 individuals globally, who satisfy the criteria for inclusion in either a cohort of “people who vape and who are nonusers of other tobacco or nicotine products” (“vapers cohort”; target N=500) or a cohort of “nonvapers who are also nonusers of other tobacco or nicotine products (“controls cohort”; target N=250), as defined in the following sections.

### Recruitment

Carefully selected recruiters, the VERITAS (Vaping Effects: Real-World International Surveillance) ambassadors (AB, [name], AM, KY, and MS), will make sure to identify and screen individuals for the VERITAS Cohort Study. The VERITAS ambassadors will pursue recruitment through social media channels, WhatsApp groups, Google email groups, posters in vape shops and universities, recommendations from other participants, and recommendations from local vape shop owners in each of the 6 geopolitical world regions (ie, Africa and Middle East, North America, Latin and South America, Asia-Pacific, Western Europe, and Eastern Europe). Ambassadors will instruct vape shop owners to ask their regular clients about their smoking history and EC use patterns to identify potential participants. The reference or control group will comprise adults who never used any tobacco or nicotine products. Control group participants will be recruited primarily among vaping individuals’ circles of friends and acquaintances. They will be matched for age and sex to the extent possible. In the event of shortfalls from this recruiting pathway, the Veritas Ambassadors will recruit further controls.

VERITAS ambassadors will be acting as the main point of contact for study participants and will be coordinated by a project leader ([name]). A document detailing the ambassadors’ roles can be found on the VERITAS Cohort website [33].

### Eligibility Criteria

Eligibility to participate in this study will be assessed by a self-complete screener questionnaire administered immediately after participants provide informed consent to participate.

#### Inclusion Criteria

Eligibility for participation in the study is determined by the following criteria. All individuals who wish to participate must be aged ≥18 years and provide informed consent to participate in the study.

The vapers cohort should meet the following inclusion criteria:

Use at least 1 of 3 types of EC or vape—disposables, rechargeable with replaceable prefilled pods or cartridges, or rechargeable and refillable with e-liquid.Have never smoked a CC *or* have smoked a CC *but* have not smoked more than 100 CCs in their lifetime [34] *and* have not smoked a CC in the past 3 months.Has never used, *or* has never used more than once a week, any of 9 other tobacco or nicotine products listed below:Traditional cigarsCigarillos or filtered cigarsSmoked tobacco in a hookahSmoked tobacco in a pipeSmokeless tobacco (including dip, spit, moist snuff, pouches, and chewing tobacco)Snus pouchesDissolvable tobaccoHeated tobacco products (eg, iQOS, Glo, and Pulze)Tobacco-free nicotine pouches

The controls cohort should meet the following inclusion criteria:

Have never used, or have never used more than once a week, any of the 3 types of EC or vaping products listed above.Same as the vapers cohort’s inclusion criterion 2.Same as the vapers cohort’s inclusion criterion 3.

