## Introduction

Electronic cigarettes (ECs) are battery-powered electronic devices that vaporize a water-soluble nicotine solution for inhalation. They do not create smoke or use combustion to operate. These consumer products have been rapidly gaining ground on combustible cigarettes (CCs) among smokers because of their potential for harm reduction from cigarette smoke and smoking cessation [1-3], their competitive price [4,5], and because of allowing people who smoke to continue having a “smoking experience without smoking” [6-8].

Considerable controversy persists surrounding the use of these products, particularly concerning potential misuse by nonsmoking youths and their potential negative impact on respiratory health [9-11]. Many studies examining nicotine vaping face challenges in data analysis due to participants having a history of CC smoking. This history might contribute to some of the adverse effects reported in prior studies, as highlighted in recent papers [12-14].

Under normal operational conditions (without overheating or dry burning coils), ECs present a significant reduction in exposure to harmful constituents compared to CCs [15-17]. No discernible negative health effects solely attributed to EC use (commonly known as “vaping”) have been conclusively established [18-20]. Analytical chemistry and toxicology studies of vaporized chemicals suggest no imminent health risks, although concerns persist about potential long-term respiratory implications [21-23]. Hence, further investigation into the prolonged health impact of persistent vaping is warranted.

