The primary aim of this study is to test the hypothesis that chronic exposure to EC aerosols does not cause an increase in respiratory symptoms among people who vape with no established cigarette smoking or other tobacco and nicotine product use history. The secondary aims are to determine the feasibility of assembling a large cohort of individuals who vape with no other established tobacco or nicotine product use history to evaluate such effects for future studies and to characterize patterns of vaping product use behavior among this unique cohort.

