#### Exclusion Criteria

Individuals who do not satisfy the criteria for inclusion in either the vapers cohort or the controls cohort will be excluded.

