### Web-Based Survey Questionnaires

After prescreening by the ambassadors, eligible individuals who consent to participate will be directed to the study website [32], where they will be subject to a 2-step verification process. When participants reach the survey platform, they will click “Don’t have an account? Register”; participants will register their email addresses. Following registration, participants will receive a “Welcome email” and a link to re-enter the survey platform, where they will be asked for their phone number to receive a confirmation code via SMS. After confirming their email addresses, they will start filling out the survey, which will consist of sociodemographic data, medical history, as well as tobacco and nicotine product use behavior. Details about the VERITAS survey document can be shared upon specific request to the corresponding author. The information collected via the web-based questionnaire will help to characterize or describe the unique cohort. Individuals will then be included in the vapers cohort or the controls cohort or they will be excluded based on their responses to questions about their past and current use of cigarettes, EC or vapes, and other tobacco and nicotine-containing products.

Individuals in the vapers cohort will then be asked questions about their historical and current patterns of use of 3 types of vaping products (ie, disposable vaping products, rechargeable prefilled pod vaping products, and rechargeable refillable vaping products). For each vaping product category, data will be collected on 12 outcomes, as applicable: (1) age of first use; (2) age of initiation, when started to vape more than once a week; (3) the number of product units used in their lifetime; (4) the number of product use days in the past 30 days; (5) length of time (eg, years or months) of vaping more than once a week; (6) nicotine content of products used; (7) flavor categories vaped more than once a week; (8) number of flavors vaped more than once a week; (9) name of favorite flavor used in the past 30 days; (10) number of product units used in the past 30 days; (11) reasons for initiating product use (free-text response); and (12) reasons for current product use (free-text response). The VERITAS survey document can be shared upon specific request to the corresponding author.

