All participants will then complete the Respiratory Symptom Experience Scale (RSES), a validated scale that asks participants to rate the frequency with which they experienced 5 respiratory symptoms in the past 30 days [35]. The 5 symptoms rated are as follows: (1) morning cough with phlegm or mucous, (2) coughing frequently throughout the day, (3) shortness of breath that makes it difficult to do normal daily activities, (4) becoming easily winded during normal daily activities, and (5) wheezing or whistling in the chest at times when not exercising or doing other physically strenuous daily activities. Rating for each symptom is made on a 5-point scale, where 1=Never (0 out of the last 30 days); 2=Rarely (1-5 days); 3=Occasionally (6-15 days); 4=Most days (16-29 days); 5=Every day (all 30 out of the last 30 days). A mean RSES score will be calculated by averaging the 5-item scores. The RSES can be found in the Multimedia Appendix 1.

Lastly, questions will assess participants’ sex, country of residence, employment status, highest educational attainment, height, and weight.

If necessary, surveys will be translated into the local language by the ambassador for countries where not all participants are fluent in English. Data will be collected on whether the participant completed the survey in English, Spanish (translation available on the platform), or their local language (in case it is determined that some questions of interest had some important difference in nuance when translated).

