### Statistical Analyses and Reporting

The primary objective of the study is to retrospectively estimate the effect of current, regular use of vaping products on respiratory symptom experience in the past 30 days, measured in this study by the mean score (0 to 5) on the 5-item RSES [35]. Details of sample size calculation and power analysis to detect differences in respiratory symptoms (ie, the RSES scores) between the “vapers cohort” and the “controls cohort” are included in Multimedia Appendix 1. In brief, with 75 participants per group, a study should be adequately powered to detect a difference of 0.57, the proposed minimal important difference, with a power of 98%. However, to detect a more conservative difference of 0.40, a study with 75 individuals per group would still have a power of 89%. The target study population will consist of approximately 500 exposed individuals and 250 matched controls–approximately 83 people who vape per each of the 6 world regions. If the initial recruitment falls short of the goal, or in the case of substantial early loss to follow-up, rolling enrollment will be considered to make up the deficit.

Data analysis of the RSES scores will be both descriptive and inferential in nature. The RSES scores and the demographic characteristics of the vapers cohort and the controls cohort will be descriptively summarized. We will test the null hypothesis that the RSES scores will not significantly differ between the vapers cohort and the controls cohort when adjusted for demographic differences. This hypothesis will be tested through a one-way between-subjects Analysis of Covariance in which the mean RSES score will be entered as the dependent variable, “Cohort” will be entered as the between-subjects independent variable, and 4 demographic variables—age, sex, education, and employment status—will be entered as covariates. Inferential and descriptive statistics will be reported for the Cohort variable adjusted for the effects of the covariates. *P* values <.05 will be considered statistically significant.

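### The primary aim concerns chronic exposure, but the vapers cohort has no minimum duration of vaping and recorded duration is only described, so the primary contrast does not by itself address chronic exposure

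*Protocol article*

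**What the plan says.** The Introduction gives the primary aim as testing that "chronic exposure to EC aerosols does not cause an increase in respiratory symptoms" in people without an established history of smoking or other nicotine use. Its rationale is in the same terms: "further investigation into the prolonged health impact of persistent vaping is warranted".

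Under Inclusion Criteria, the exposure requirement for the vapers cohort is "Use at least 1 of 3 types of EC or vape". No duration is attached. The controls' counterpart is "Have never used, or have never used more than once a week, any of the 3 types of EC or vaping products". Exclusion Criteria adds no duration rule: "Individuals who do not satisfy the criteria for inclusion in either the vapers cohort or the controls cohort will be excluded".

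Statistical Analyses and Reporting words the target differently, as the effect of "current, regular use of vaping products on respiratory symptom experience in the past 30 days". The primary model there is an ANCOVA of the mean RSES score on cohort, with age, sex, education and employment status as covariates.

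Under Web-Based Survey Questionnaires, vapers report, for each of three product categories, the "length of time (eg, years or months) of vaping more than once a week". The analysis section assigns this item to the secondary objective, which is descriptive only. Further filtered or stratified analyses are optional, and duration is not named among them.

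**The concern.** The aim and the exposed group do not match. As the criteria are printed, a person who took up vaping a few weeks ago qualifies and counts in the primary comparison exactly as someone who has vaped for years. The RSES asks participants to "rate the frequency with which they experienced 5 respiratory symptoms in the past 30 days". For someone who started 14 days ago, 16 of those 30 days would predate any vaping.

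What is at stake is interpretation. Under the stated aim, the adjusted cohort difference would be reported as evidence on chronic exposure, although it averages over an unspecified mix of durations. Because the hypothesis is one of no increase, a small or null difference would be read as supporting it. The limitations listed in the Discussion (cross-sectional design, self-selection, self-report, language and culture) do not mention duration.

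**Working it through.** **Step 1: the text.**

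| Element | Where | What it fixes about duration |
|---|---|---|
| Primary aim | Introduction | Chronic exposure |
| Vapers criterion 1 | Inclusion Criteria | Use of a product; no minimum |
| Exclusions | Exclusion Criteria | Nothing further |
| Analysis target | Statistical Analyses and Reporting | Current, regular use |
| Duration item | Web-Based Survey Questionnaires, item 5 | Collected per product category |
| Use of that item | Statistical Analyses and Reporting | Descriptive only |

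The same list of criteria does set thresholds elsewhere: 100 lifetime cigarettes, none in the past 3 months, and other products never more than once a week. Recruitment through regular vape-shop clients is one channel among several and is not an eligibility rule.

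**Step 2: the plan's own power figures.** The article states 98% power for a difference of 0.57 and 89% for 0.40, with 75 per group. It does not print the SD, so I solved for it, assuming a two-sided 5% test and the normal approximation: SD = Δ / [(1.960 + z_power) × √(2/75)].

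- From 0.40 and 89%: 0.40 / [(1.960 + 1.227) × 0.1633] = 0.77.
- From 0.57 and 98%: 0.57 / [(1.960 + 2.054) × 0.1633] = 0.87.

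A single SD between about 0.74 and 0.79 brings both statements within 2 percentage points (SD 0.769 gives 99.5% and 89.0%), so the power statement is not shown to be wrong. I carry both 0.77 and 0.87 forward as a range.

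**Step 3: effect of mixing durations.** Let Δ be the difference for long-term vapers, Δr the difference for recent starters, and f the share of recent starters. Then

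observed difference = (1 − f)Δ + fΔr, and observed − Δ = f(Δr − Δ).

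The shift is toward zero when 0 ≤ Δr < Δ and away from zero when Δr > Δ. With Δr = 0 (assumed), the observed difference is (1 − f)Δ. The article gives no value for f, so a range is shown:

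| f | true 0.57 becomes | true 0.40 becomes |
|---|---|---|
| 10% | 0.51 | 0.36 |
| 20% | 0.46 | 0.32 |
| 30% | 0.40 | 0.28 |
| 50% | 0.29 | 0.20 |

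**Step 4: power at the target size.** SE = SD × √(1/500 + 1/250) = SD × 0.0775, which is 0.060 for SD 0.77 and 0.067 for SD 0.87. The difference detectable with 80% power is (1.960 + 0.842) × SE, about 0.17 to 0.19. For a true 0.40, power is 98.6–99.7% at f = 30% and 84–92% at f = 50%. It falls below 80% only when f exceeds 1 − 0.19/0.40 to 1 − 0.17/0.40, about 53–58% before rounding. For a true 0.57 the corresponding f is about 67–71%.

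**Step 5: precision of a duration-restricted comparison.**

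- 20% of vapers dropped: √[(1/400 + 1/250) / (1/500 + 1/250)] = 1.041.
- 30% dropped: √[(1/350 + 1/250) / (1/500 + 1/250)] = 1.069.

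**The case against.** The strongest reply is that the analysis section already targets current, regular use, so the ANCOVA answers its own stated question and only the wording of the aim is out of line. That largely stands. It is why the primary set need not change, but the aim remains the sentence against which results will be read.

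A reader might go further and infer that the design is biased toward its hypothesis of no increase. The documents do not support that as a fact. It requires recent starters to show a smaller effect than long-term users. Early cough or irritation in new users would move the difference the other way.

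A reader might also infer that a null result would be worthless, or that the study loses its power. Neither is shown. The share of recent starters is unknown, and the sample absorbs considerable dilution.

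Nor is it certain that very recent starters were enrolled. The screener is in an appendix that is not shown, and cohorts are assigned from answers on past and current use. No duration floor appears in the printed criteria, however.

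Finally, one might want a 12-month minimum to define the primary set. No such threshold has a basis in the documents. Enrolment is complete, so the change could be data-aware. Keeping only long-term current users may also select people who tolerate vaping, which could itself favour a finding of no increase. Those objections stand against replacing the primary set, but not against a pre-specified sensitivity analysis. Duration is also not an ordinary covariate in a vaper–control model, since controls have no regular-vaping duration. It belongs in an analysis within vapers.

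**Conclusion.** The mismatch is real. The aim claims chronic exposure, the printed criteria admit any duration, the analysis section says current, regular use, and the one item that could connect them is only described. The primary contrast is a comparison of current vapers of mixed duration with controls, and it should be reported as that.

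The numerical consequence is conditional. If recent starters show no effect, the difference is multiplied by (1 − f), for example from 0.57 to 0.46 at f = 20%. Both f and the size and sign of the effect in recent starters are assumptions. The problem is one of interpretation and possible bias in the estimate. Power at 500 and 250 is not the issue unless more than about half the vapers are recent starters. That last statement rests on back-solved SDs of 0.77 to 0.87, a two-sided 5% test and no covariate adjustment.

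**What to change.** 1. Reword the primary aim to current, regular vaping, in line with the analysis section, and state what regular means, since vapers criterion 1 does not define it. Keep all eligible vapers in the primary ANCOVA.
2. Before RSES scores are examined by duration, pre-specify a sensitivity analysis that repeats the ANCOVA in vapers above stated minimum durations, for example 6, 12 and 24 months. Item 5 is recorded per product category, so give a combining rule: the longest duration across the three categories. State how vapers with no period of vaping more than once a week are handled.
3. Pre-specify a within-vapers analysis of RSES by duration.
4. Base any statement about chronic exposure on items 2 and 3, and say that restriction to long-term users may select people who tolerate vaping.

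The cost is some wording and a little extra analysis on data already collected. The restricted comparison has a standard error about 4–7% larger if 20–30% of the vapers are dropped. The primary comparison is unchanged.

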**Methods:**

This will be a multicountry, cross-sectional internet-based survey of 750 adults aged ≥18 years who satisfy the criteria for inclusion in either a cohort of people who exclusively vape and who are nonusers of other tobacco or nicotine products (“vapers cohort”; target N=500) or a cohort of nonvapers who are also nonusers of other tobacco or nicotine products (“controls cohort”; target N=250). The primary end point of the study is the RSES score. RSES scores of people in the “vapers cohort” will be compared with those of people in the “controls cohort.” Additionally, the study will collect data to characterize patterns of vaping product use among the vapers cohort. Data collection will include information about the age initiation of using vape products, reasons for starting and continuing the use of vape products, specific types of products used, flavors and nicotine strengths of recently used products, as well as the frequency and intensity of product use in the past 30 days.

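### Criterion 3 admits current use of other tobacco products, four of them smoked, at up to once a week, so the nonuser and exclusive-vaper labels do not hold and the primary model does not account for it

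*Protocol article*

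**What the plan says.** Criterion 3 (Protocol article, Inclusion Criteria) admits a vaper who has never used, or who "has never used more than once a week, any of 9 other tobacco or nicotine products listed below". The controls' list repeats the rule: "Same as the vapers cohort’s inclusion criterion 3". The nine products include traditional cigars, cigarillos or filtered cigars, hookah tobacco and pipe tobacco, all of which are smoked.

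Criterion 2, which also covers both cohorts, treats cigarettes differently. A participant who has ever smoked must "have not smoked more than 100 CCs in their lifetime" and must also "have not smoked a CC in the past 3 months".

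Elsewhere the cohorts are described more strictly:

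- Abstract, Methods: the vapers are "people who exclusively vape and who are nonusers of other tobacco or nicotine products".
- Population: the cohorts are "people who vape and who are nonusers of other tobacco or nicotine products" and "nonvapers who are also nonusers of other tobacco or nicotine products". The Abstract's Objective uses the same idea.
- Recruitment: "The reference or control group will comprise adults who never used any tobacco or nicotine products".
- Study End Points: the controls are people who have neither vaped nor smoked at any time.

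The Introduction's statement of aims and the Abstract's Conclusions are softer and speak only of no established use of other products.

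The primary analysis (Statistical Analyses and Reporting) is an ANCOVA of the mean RSES score on cohort, with age, sex, education and employment status as covariates.

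**The concern.** The RSES asks about cough, breathlessness and wheeze over the past 30 days. Tobacco smoke inhaled in those same 30 days is the exposure that the study most needs to keep out. The Introduction says as much: it argues that smoking confounds vaping research, that crude binary measures leave residual confounding, and that cleaner data are needed.

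Criterion 2 keeps recent cigarette smoke out. Criterion 3 lets recent smoke from cigars, pipes and hookahs in, provided it stays at or below the weekly cap. Two things are at stake. The contrast may partly reflect differences in other tobacco use. The published description of who was compared would also be inaccurate, whatever the estimate turns out to be.

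**Working it through.** No figure in the article has to be reproduced here. The check counts what the criteria allow and then sets the descriptions side by side.

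**Inputs.** Products listed: 9, of which 4 are smoked. Cap: once a week. Recall period: 30 days (Web-Based Survey Questionnaires). Cigarette window: 3 months, taken as 13 weeks.

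**Ceiling on admitted use** = (uses per week) × (weeks in the period).

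| Reading of the cap | Per week | In 30 days | In 13 weeks |
|---|---|---|---|
| Combined across products | 1 | 1 × 30/7 = 4.3 | 13 |
| Per product, four smoked products | 4 | 4 × 30/7 = 17.1 | 52 |
| Per product, all nine | 9 | 9 × 30/7 = 38.6 | 117 |
| Cigarettes (criterion 2) | – | 0 | 0 |

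Even the first row, the narrowest reading, leaves current smoke exposure in the recall period.

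**Labels against criterion 3.** Take a person who now smokes a pipe once a week and has never exceeded that.

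- Criterion 3: eligible for either cohort.
- Nonuser of other products (Abstract, Population): not met.
- Exclusive vaper (Abstract, Methods): not met.
- Control who never used any product (Recruitment): not met.
- Control who never smoked (Study End Points): not met.
- No established use (aims): arguably met.

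**Effect on the contrast.** Let pV and pC be the proportions of current users among vapers and controls, and δ the mean RSES excess due to that use. If δ is the same in both cohorts and the covariates do not capture the use, then

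bias in (vapers − controls) ≈ (pV − pC) × δ.

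The article gives none of the three quantities. Only the difference in prevalence matters, so equal use in the two cohorts cancels. If δ is positive, extra users among controls raise the reference mean and move the result towards the hypothesis of no increase; extra users among vapers move it the other way.

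The internal conflict could itself create a difference. If controls were recruited under the never-used wording in Recruitment while vapers were admitted under criterion 3, pC would be near 0 and pV would not.

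For scale only: with an assumed gap of 20 percentage points, a shift of 0.40 (the smaller difference in the power statement) would need δ = 0.40/0.20 = 2.0 on items scored 1 to 5. That illustrates the formula and does not estimate the bias.

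**The case against.** The best defence is that the aim concerns people with no established history of other use. A never-more-than-weekly rule is a plausible way to define established use, parallel to the 100-cigarette rule. The rule is the same in both cohorts, so it does not by itself favour one side. The screener is in an appendix that is not shown and may be more specific. Much of this stands: it removes any claim about the direction or size of bias. It does not reconcile criterion 3 with the nonuser and never-used descriptions, nor does it explain why recent cigarettes exclude and recent cigars do not.

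Several stronger readings are tempting, but the documents do not support them:

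- A reader might infer that someone smoking tobacco four times a week is certainly admitted. That needs the cap to run product by product, which is a natural reading but is not spelled out. The survey's category-by-category questions concern vaping products and support it only by analogy. Even then, four a week is a ceiling and not a typical participant.
- A reader might infer that current use is unlimited. It is not, because a rule of never more than once a week also binds the present. What is missing is an abstinence window.
- A reader might object that the rule needlessly excludes people with brief, heavier use long ago. Since the protocol argues that past tobacco use may leave unknown effects, excluding them is consistent with its rationale.

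**Conclusion.** The point holds in a limited form. On any reading, both cohorts can include people who currently smoke a non-cigarette tobacco product once a week, about 4 sessions in the recall period. On a per-product reading the ceiling for the four smoked products is about 17. That contradicts the descriptions in the Abstract, Population, Recruitment and Study End Points, and the planned ANCOVA does not account for such use. Adding a covariate could reduce confounding but would not make these participants nonusers.

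The bias cannot be sized from the article. Prevalence in each cohort, the effect of such use on RSES and the SD are all unstated, and only a difference in use between cohorts would bias the contrast. The finding is about an inconsistent definition and an uncontrolled exposure; it does not show that the result is wrong.

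**What to change.** 1. State whether the once-a-week cap in criterion 3 applies to each product or to the nine combined.
2. Reconcile the cohort descriptions in the Abstract (Objective and Methods), Population, Recruitment and Study End Points with criterion 3, and say which definition was applied when controls were recruited.
3. Enrolment closed at 748, so work in the analysis. The Web-Based Survey Questionnaires section says that answers on past and current use of other products are collected. Use them to run the RSES comparison in participants with no current use of any of the nine products, taking the past 3 months or the nearest window that the survey recorded. The article does not confirm that a 3-month window was asked.
4. Report the as-enrolled comparison alongside it, labelled for what it is, such as at most weekly use of other products, and give the number of current users in each cohort.

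A lifetime cap on the nine products combined should not be added. It would remove more past users without addressing current exposure.

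The cost is a redefined analysis set, corrected wording and some loss of precision. If a fraction f of each cohort is dropped, the standard error grows by about 1/√(1 − f): 1/√0.95 = 1.03 for an assumed 5% and 1/√0.80 = 1.12 for an assumed 20%. No new recruitment is needed.
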